***Anthropometric measures***				
Height	✓	✓	✓	Measured to the nearest 0.1 cm at least twice
Weight	✓	✓	✓	Measured to the nearest 0.1 kg at least twice
Waist and hip circumference	✓	✓	✓	Measured to the nearest 0.1 cm at least twice
Blood pressure	✓	✓	✓	Measured to the nearest 1 mm Hg. The average of the last two of three measurements
Visual acuity	✓	✓	✓	The distance vision test must be performed in both eyes separately, the right eye first and then the left eye
Diopter	✓	✓	✓	The test should be performed using a desktop automated computerized optometrist and should be averaged 3 times per eye
Body composition	✓	✓	✓	The body composition analyzer adopts a 4-point contact electrode for measurement
***Biological samples***				
Blood	✓	-	✓	Collect 5 ml of venous blood
Saliva	✓	-	✓	Collection of 10 ml of mid-stream urine
Urine	✓	-	✓	Collect 5 ml of saliva
***Measurement of indoor environmental indicators***				
Household air pollution exposure	✓	-	✓	Continuous measurement with illuminometer for 7 days
Night light exposure	✓	-	✓	7 consecutive days of measurement with sensors
***Questionnaire***	✓	-	✓	
Student Questionnaire	✓	✓	✓	Issues related to children and adolescents
Parental Questionnaire	✓	✓	✓	Issues related to parents and children
School Questionnaire	✓	✓	✓	School related issues

Anthropometric measures includes visual acuity, refraction,height, weight, waist circumference, hip circumference, blood pressure, blood routine, and body composition, and 5% of the samples were randomly selected for morphological index analysis measurement.

Biospecimen measures consisits of blood, urine of saliva. All biological samples were collected after fasting for 12 h, and biochemical analysis of all biological samples was performed by a biomedical analysis company accredited by Peking University.

Environmental measurements household air pollution exposure and nighttime light exposure.

Questionnaire will be utilized to assess the behaviors of children and adolescents, as well as school policies for the prevention and management of myopia and obesity, along with other possible moderators/mediators of intervention. The questionnaire has been developed based on previous research and pilot studies, and is deemed feasible for this study, as well as acceptable to both children and adolescents and their parents. For children in grades 1–4, parental assistance will be provided to complete the questionnaire, whereas students in grade 7 will receive guidance from their class teacher when filling out the questionnaire.The parent questionnaire will focus on parental information and health behaviors, while the school questionnaire will cover basic information, myopia and obesity intervention work, personnel management, health education, sports activities, nutrition, and classroom environmental sanitation supervision. The trained project members will provide detailed explanations of the questionnaires, and assistance and guidance will be given as needed to complete them effectively. The project team staff will review 3% of the questionnaires within one week.

### Outcomes

#### Primary outcome

The primary outcome of this study is to assess the differences in changes in visual acuity and body mass index between children and adolescents 12-month after baseline as evaluated by medical examination. Between-group differences in changes in outdoor activities screen time, fruit and vegetable intake, high-quality protein intake, sugar beverage consumption, sleep duration, and supervision will be assessed using questionnaires.

(‘2’). Engage in at least 2 h of outdoor physical activity during the day, with at least 1 h of moderate to high intensity exercise.

(‘2’). Limit screen time to no more than 2 h per day.

(‘5’). Consume 5 servings of fruits and vegetables, each equivalent to an adult’s fist, daily.

(‘1’). Consume 1 serving of lean meat, equivalent to an adult’s hand, daily.

(‘0’). Avoid sugary drinks.

(‘S’). Ensure adequate sleep, with elementary school children needing 10 h and junior high school students needing 9 h of sleep each night.

(‘S’). Parents and students should provide timely feedback and cooperate with efforts to prevent and control myopia and obesity.

#### Secondary outcomes

Secondary outcomes will be evaluated using the RE-AIM framework to comprehensively assess the acceptability, feasibility, adoption, usage, and maintenance of the intervention study.

(‘Reach’). We will assess the reach of the program by measuring the number of individuals who expressed willingness to participate,

(‘Effectiveness’). The effectiveness of the intervention, including why and how it worked, or did not work.(‘Adoption’). We will examin the adoption of the program by students, parents, and schools, as well as the likelihood and reasons for willingness to accept the intervention in the future.

(‘Implementation’). Whether the elements of the intervention were actually accepted by the study participants and the school as an indication of whether the achievement of the desired outcomes of the myopia and obesity intervention was due to the content of the intervention itself or the way in which the intervention was implemented.

(‘Maintenance’). We will evaluate the maintenance of the intervention by analyzing how well the behavior was maintained after the intervention ended and whether it became a daily practice and policy in the school.

### Sample size

In our study, we aimed to investigate the co-morbidity of myopia and obesity among Beijing children and adolescents. Based on previous studies, the co-morbidity rate was expected to be 17.3% in the intervention group and 13.5% in the control group, setting a two-sided α = 0.05 and a 90% certainty. Using the PASS15 software, the sample size N1 = 1891 cases for the intervention group and N2 = 1891 cases for the control group were obtained according to the formula $$( {\text{n}}=\frac{2\overline{p }\overline{q }{\left({\text{Z}}_{\alpha }+{\text{Z}}_{\beta }\right)}^{2}}{{\left({\text{p}}1-{\text{p}}2\right)}^{2}} )$$ to the randomized controlled trial, taking into account the loss and refusal of 20% of the cases, at least 2250 cases each for the intervention and control groups were finally required, and at least 4500 cases were included in total.

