**Methods and analysis:**

This study aims to develop a comprehensive intervention strategy "22510SS" based on the socio-ecological model, and A two-arm cluster randomized trial with a parallel-group of a 1:1 allocation ratio in 36 primary and secondary schools to test its evidence-based intervention programs on the effects and implementation of myopia and obesity epidemics in children and adolescents in grades 4 and 7. The primary outcomes will include differences in visual acuity, body mass index, outdoor activity indicators, screen time, fruit and vegetable intake, high-quality protein intake, sugar-sweetened beverage intake, sleep duration, and level of monitoring among children and adolescents. Secondary outcomes will assess the acceptability, feasibility, uptake, use, and maintenance of the intervention. Effects on the primary and secondary outcomes will be analyzed using linear and logistic regression analyses, as well as difference-in-difference analysis, taking into account cluster effects and possible confounding factors. Process assessments will also be conducted through quantitative and qualitative analyses, including acceptability, feasibility, gender, adoption, implementation, and sustainability.

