### Effectiveness evaluation

#### Study design

A two-arm cluster randomized trial with a parallel-group of a 1:1 allocation will be conducted in three districts (Dongcheng District, Tongzhou District, and Changping District) according to their geographical location and socioeconomic conditions in Beijing and then selected schools in the districts for a 12- month intervention. In each of the three districts, 3 primary schools (grades 1–4), 3 junior high schools (junior 1), and a total of 18 schools will be selected as intervention schools, while other 18 schools will be regarded as control schools. t. Children and adolescents grades 1–4 and 7 with aged 6–14 years will be recruited for advoiding missing follow-ups due to further education into other schools (Fig. 4). All intervention schools in the three districts will use a standardized and uniform research protocol.

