### Statistical analyses

For the qualitative data, we will use Excel 2016 for data input and SPSS 25.0 for statistical analysis. Statistics will include score mean, standard deviation, coefficient of variation, etc. The key basis will be whether it will be used as a common intervention concept for the prevention of comorbidities. Experts will score items with a mean greater than 3.5 and a coefficient of variation less than 0.25. Items will be selected, and the item descriptions will be modified regarding expert suggestions.

For quatitative data, we will double entere by using Epidata 3.1 analyze using SPSS 25.0. The primary outcome will be group differences in changes in visual acuity and body mass index in children and adolescents at 12-month after the baseline. We will use a mixed-effects model to compare the group difference, taking school into account due to its cluster effect. Then we will conduct subgroup analysis to identify the interaction effect (stratification factor × group) and analyze the differences in intervention effects between strata. Furtherly, we will use difference-in-difference analysis to analyze differences between the intervention and control groups before and after the implementation of the intervention. The secondary outcomes will be analysed in the similar steps. All statistical tests will be two-sided at the 5% level of significance.

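### The sample size is computed for individually randomised pupils although whole schools are randomised, so the stated 90% power does not hold with 36 schools

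*Protocol article*

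**What the plan says.** **Design.** The abstract describes a "cluster randomized trial with a parallel-group of a 1:1 allocation ratio in 36 primary and secondary schools". The Study design section confirms that "a total of 18 schools will be selected as intervention schools", "while other 18 schools will be regarded as control schools". Each arm therefore has 18 clusters: three districts, each supplying three primary and three junior high schools.

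**Sizing.** The Sample size section expects that "the co-morbidity rate was expected to be 17.3% in the intervention group and 13.5% in the control group". It sets a two-sided 5% level and 90% power, prints a pooled two-proportion formula, and reports that "the sample size N1 = 1891 cases for the intervention group and N2 = 1891 cases for the control group were obtained". It then allows 20% for loss and refusal, which brings the requirement to at least 2,250 per arm and 4,500 in total. The section mentions no ICC, design effect, cluster size or number of schools.

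**Analysis.** The Statistical analyses section under Effectiveness evaluation specifies a mixed-effects model, "taking school into account due to its cluster effect".

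**The concern.** Pupils in the same school share teachers, canteen, timetable and neighbourhood, so their outcomes are correlated. When schools are randomised, this correlation inflates the variance of the between-arm comparison. The planned model will carry that inflation into its standard error, but the sample size does not. The two sections therefore describe different trials: one with about 3,800 independent pupils, the other with 36 schools.

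The 90% figure is the only power statement in the article. A reader who trusts it would take a null co-morbidity result as good evidence against a 3.8-point difference. In fact the trial may have had even odds or worse of detecting that difference.

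**Working it through.** **Inputs from the article.** p1 = 0.173, p2 = 0.135, difference 0.038; two-sided α = 0.05 and power 0.90, so (1.960 + 1.282)² = 10.507; 1,891 per arm before loss; 2,250 per arm after the loss allowance; 18 schools per arm.

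**Input not in the article.** The ICC. The values 0.005 to 0.05 are an assumption, shown as a range.

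**Step 1: reproduce the stated figure.**
- Variance sum: V = 0.173 × 0.827 + 0.135 × 0.865 = 0.25985.
- Unpooled form: n = V × 10.507 / 0.038² = 1,890.8, which rounds up to 1,891.
- Printed pooled form: p̄ = 0.154, so n = 2 × 0.154 × 0.846 × 10.507 / 0.038² = 1,896.

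The stated 1,891 is the individual-randomisation answer with a design effect of 1.

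**Step 2: check whether the 20% uplift hides a design effect.** The text assigns it to loss and refusal, and it does not fully cover even that. 1,891 / 0.8 = 2,364, not 2,250. 2,250 × 0.8 = 1,800, which gives 88.5% power with no clustering at all.

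**Step 3: power with clustering.** With mean cluster size m = n/18:
- DE = 1 + (m − 1) × ICC
- n_eff = n / DE
- power = Φ(0.038 / √(V / n_eff) − 1.96)

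Example: n = 1,891, m = 105, ICC = 0.01. DE = 2.04, n_eff = 927, SE = √(0.25985 / 927) = 0.01675, and power = Φ(2.27 − 1.96) = 62%.

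| ICC (assumed) | DE at m = 105 | Power, 1,891 per arm | Power, 1,800 per arm (2,250 less 20%) | Power, all 2,250 per arm |
|---|---|---|---|---|
| 0 | 1.00 | 90% | 89% | 94% |
| 0.005 | 1.52 | 75% | 73% | 79% |
| 0.01 | 2.04 | 62% | 61% | 66% |
| 0.02 | 3.08 | 45% | 45% | 47% |
| 0.05 | 6.20 | 26% | 25% | 26% |

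With 2,250 per arm all analysed, power stays at 90% only while the ICC is at most about 0.0015. A t reference on 34 degrees of freedom (36 schools less 2) takes off roughly another 1 to 2.5 points.

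**Step 4: unequal cluster sizes.** On the Study design section's reading, primary schools supply grades 1–4 and junior high schools one grade. An illustrative 200 versus 50 pupils per school gives 9 × 200 + 9 × 50 = 2,250 per arm, mean 125, SD 75, CV = 0.6. With DE = 1 + ((1 + CV²)m − 1) × ICC and 1,891 per arm, power becomes 70%, 55%, 38% and 21% at ICC 0.005, 0.01, 0.02 and 0.05.

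**Step 5: detectable difference at 90% power.** (1.960 + 1.282) × √(V / n_eff), with V held at its planned value and 1,891 per arm in equal clusters, gives 3.8 points at ICC 0, 5.4 at 0.01, 6.7 at 0.02 and 9.5 at 0.05.

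**Step 6: ceiling from the number of schools.** As m grows, n_eff tends to 18 / ICC. Setting 18 / ICC = 1,891 gives ICC = 0.0095. Above that value, adding pupils cannot reach 90%. With unlimited pupils per school, power is capped at about 61% for ICC 0.02 and 29% for 0.05.

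**The case against.** The core point is hard to contest, because the article prints its formula, inputs and result. Condensation of a fuller protocol does not explain them: a design effect applied elsewhere could not leave 1,891 unchanged. Several qualifications deserve a hearing.

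- **No ICC is given.** The size of the loss is therefore conditional, and with full retention 90% survives a very small ICC. This stands, but at 1,891 per arm any positive ICC takes power below 90%.
- **1,891 is not exactly the output of the printed formula.** This is correct: the pooled form gives 1,896 and the unpooled form 1,891. Neither contains clustering.
- **The powers concern co-morbidity.** The Primary outcome section names changes in visual acuity and BMI instead. This stands as a limit on scope: nothing here gives the power for those outcomes. Co-morbidity is nevertheless the endpoint to which the article attaches its 90%.
- **The 4:1 cluster imbalance depends on which grades are recruited.** The abstract says grades 4 and 7, which would make clusters more equal. The CV 0.6 row is conditional on the Study design reading; the main table does not need it.
- **2,250 is a minimum.** The class-recruitment rule allows about 41–78 pupils per grade. With 9 × 4 + 9 × 1 = 45 grade groups per arm, the upper end is 3,510, or 2,808 after 20% loss. Power is then about 84% at ICC 0.005 and 70% at 0.01, still below 90%.
- **Covariate adjustment could lower the effective ICC.** Adjusting for baseline, district or school level might recover some power, but the sample size section claims no such gain.
- **The analysis itself is not invalid.** The planned model allows for school. The fault lies in the power claim, not in the test.

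**Conclusion.** The concern holds. The sample size omits the design effect that the trial's own allocation and analysis require, and the 90% power does not belong to this design. On the plan's own rates and 1,891 evaluable per arm in equal clusters, power is about 75% at ICC 0.005 and falls to 26% at 0.05. The detectable difference at 90% power rises from 3.8 to between 5.4 and 9.5 points for ICC 0.01 to 0.05. Unequal school sizes would make this worse. The direction is certain for any positive ICC at 1,891 per arm; the magnitude rests on the assumed ICC range and applies to the co-morbidity endpoint only.

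**What to change.** Keep the 36 schools and restate what they can deliver.

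1. Delete the statement that 1,891 (or 2,250) per arm gives 90% power.
2. Compute the effective sample size per arm as n / [1 + ((1 + CV²)m − 1) × ICC], with 18 schools per arm, the evaluable number expected after loss, and the expected variation in school size.
3. Report power for the 3.8-point difference and the minimum detectable difference over a stated ICC range, for example 0.01 to 0.05, with the basis for that range. As a pattern: with 18 schools and 1,800 evaluable pupils per arm in equal clusters, power is about 61%, 45% and 25% at ICC 0.01, 0.02 and 0.05.
4. State that these figures refer to co-morbidity, and settle which grades are recruited so that m and CV can be fixed.

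The cost is rewording of one section, with no additional schools or pupils. The price is a stated power that is plainly lower than the one now printed.

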### Recruitment

#### Recruitment of the schools

For the schools participating in the program, the size of a class was varying from 30 to 50 children and adolescents per class. If the number of children and adolescents in one class is less than 40, we will recruit two classes from the corresponding grade, and if the number of children and adolescents is greater than 40 of one class, we will recruit one class. School inclusion criteria are: 1) School principals should agree and cooperate with the project team to implement the intervention plan, and the school has health related human resources itself, such as school doctors, health teachers, and physical education teachers; 2) The total number of children and adolescents in each grade should be larger than 50. School exclusion criteria are: 1) Boarding schools and specialty schools for children and adolescents with talents or minority ethnic groups will be excluded; 2) Schools will also not be included if they have a definite plan for relocation or cancellation in the next 1 year.

Four steps will be applied for the recruitment of the schools. First, the education authority of each district will be contacted through a project workshop to seek their input on the study proposal. Second, the education authorities of each district will provide basic information on the participating schools (school type, number of children and adolescents, and teachers). Third, project team will hold school seminars to understand the specific situation of the school, conduct field visits to the school, and finally determine the selected school for the project. Fourth, the final list of eligible schools and classes will be determined by the principal investigator, and schools will be invited to participate in the study by the project partners.

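### The 20% loss allowance is miscalculated: 2,250 pupils per arm leave 1,800 evaluable, not the required 1,891

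*Protocol article*

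**What the plan says.** The Sample size section prints the whole chain. On the rates, "the co-morbidity rate was expected to be 17.3% in the intervention group and 13.5% in the control group". The error rates follow: "setting a two-sided α = 0.05 and a 90% certainty". The result is "the sample size N1 = 1891 cases for the intervention group and N2 = 1891 cases for the control group". The allowance comes next: "taking into account the loss and refusal of 20% of the cases, at least 2250 cases each for the intervention and control groups". The total is given as "at least 4500 cases were included in total".

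On who is recruited, the abstract (Methods and analysis) describes "children and adolescents in grades 4 and 7" in 36 schools. The body (Study design) says: "Children and adolescents grades 1–4 and 7 with aged 6–14 years will be recruited". The inclusion criteria under Recruitment procedure of the study population repeat grades 1–4 or 7. Under Recruitment of the schools, classes hold 30 to 50 pupils. Two classes per grade are taken where a class has fewer than 40, and "if the number of children and adolescents is greater than 40 of one class, we will recruit one class".

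**The concern.** An allowance for loss has one job: after the assumed loss, the number needed for analysis must remain. Here the need, the loss rate and the inflated number stand together in one section, and they do not agree. The inflated number is worded as a minimum, so it is the figure that recruitment would be held to. If the trial enrols exactly that minimum and loses exactly the share it planned for, it falls short of its own requirement. Any later power statement that allows for schools as clusters would also start from the wrong evaluable number.

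The grade mismatch is a smaller matter. A reader of the abstract and a reader of the body would come away with different study populations.

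**Working it through.** **Inputs.** From Sample size: rates 0.173 and 0.135, two-sided α = 0.05, power 90%, 1,891 per arm before loss, 20% loss and refusal, 2,250 per arm, 4,500 in total. From Study design: 9 primary and 9 junior high schools in the intervention arm (3 of each in 3 districts) and 18 control schools. From Recruitment of the schools: the class sizes and class rule.

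**Step 1: reproduce 1,891.** (1.960 + 1.282)² = 10.507 and (0.173 − 0.135)² = 0.001444.
- Unpooled variance: 0.173 × 0.827 + 0.135 × 0.865 = 0.259846. Then 0.259846 × 10.507 / 0.001444 = 1,890.8, so 1,891.
- Pooled formula as printed: 2 × 0.154 × 0.846 = 0.260568. Then 0.260568 × 10.507 / 0.001444 = 1,896.

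The base figure reproduces for its stated inputs, so the error lies in the next step.

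**Step 2: inflate for 20% loss.**
- Required form, n/(1 − d): 1,891/0.80 = 2,363.75, so 2,364 per arm and 4,728 in total.
- Common shortcut, n × (1 + d): 1,891 × 1.2 = 2,269.2, so 2,270 per arm.
- Stated: 2,250 per arm. This is 114 per arm (228 in total) below the first and 20 per arm below the second.

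**Step 3: read 2,250 backwards.**
- Evaluable at 20% loss: 2,250 × 0.80 = 1,800, and 1,891 − 1,800 = 91 short per arm.
- Loss that 2,250 can absorb: 1 − 1,891/2,250 = 0.160.

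**Step 4: power at 1,800 per arm, without clustering.** Power = Φ[(Δ − 1.960 √(2p̄q̄/n)) / √((p₁q₁ + p₂q₂)/n)].
- n = 1,800: (0.038 − 1.960 × 0.01203)/0.01201 ≈ 1.200, so power is 0.885.
- n = 1,891: the same formula gives 0.900.

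**Step 5: pupils available under each statement of the grades.** This counts pupils before refusals and exclusions. It assumes that the control schools have the same primary and junior high mix as the intervention schools. One school-grade yields 41–50 pupils (one class over 40) or 60–78 (two classes of 30–39).

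| Grades | School-grades | Pupils | Needed per school-grade for 4,500 |
|---|---|---|---|
| 4 and 7 (abstract) | 36 | 36 × 41 = 1,476 to 36 × 78 = 2,808 | 125 |
| 1–4 and 7 (body) | 18 × 4 + 18 = 90 | 90 × 41 = 3,690 to 90 × 78 = 7,020 | 50 |

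The 2,808 is not a strict ceiling. The rule can be read as triggered by one class under 40, and a pairing of 39 + 50 then gives 36 × 89 = 3,204. Classes of exactly 40 are not covered by the rule; two of them would give 36 × 80 = 2,880. All of these lie below 4,500.

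**The case against.** The strongest reply is that the error is too small to matter. The figure of 2,250 is within 1% of the shortcut value 2,269, which suggests that shortcut rounded down, although the document does not say so. The cost is about 1.5 points of power. The target is a floor, so more pupils may be enrolled, and the body's grades could supply 4,728. All of this is fair, and it limits the weight of the point. It does not repair the figure: a minimum cannot be rounded down below the number it protects, and neither way of inflating gives 2,250.

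A second reply is that the base itself needs more than this repair. It rests on co-morbidity rates, whereas the primary outcome is change in visual acuity and body mass index. It shows no design effect, although the analysis models school as a cluster. The rate entered for the intervention arm is also the higher one. On this view, correcting one step tidies a number that has to be recalculated anyway. That stands as a reason to correct the allowance as part of a wider restatement, not as a reason to leave it.

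On the grades, a reader might infer from Step 5 that the trial cannot reach its enrolment. The documents do not support this. The Sample size section ties 4,500 to no particular grades, and the design, eligibility and questionnaire text all use grades 1–4 with grade 7. Those grades can supply the number if school-grades average at least 50 participating pupils. The abstract is the only outlier.

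**Conclusion.** The point holds for the loss allowance. The stated minimum is short by 114 pupils per arm (228 in total, 4.8% of 4,728). It meets the 90% requirement only if loss is at most 16.0%. The 88.5% rests on the plan's own rates and on independent observations, so it isolates the effect of this one step. It is not an estimate of the trial's real power, which clustering would lower further. It would also be too strong to say that this error alone leaves the trial seriously underpowered.

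The grade mismatch is a one-phrase inconsistency between abstract and body. The supply figures show only that the abstract's wording does not fit the enrolment target, given the class rule and an equal mix of schools in the two arms.

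**What to change.** In Sample size, choose one of two statements:
1. 2,364 per arm, 4,728 in total, for 20% loss and refusal.
2. Keep 4,500, and state that 20% loss leaves 1,800 evaluable per arm with about 88.5% power before clustering, and that 90% is reached only if loss is at most 16%. The 16% should be reported as a consequence and not adopted as the assumed loss, because the document gives no evidence for it.

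If 4,500 is kept, carry 1,800 per arm into any power statement that allows for clustering. In the abstract, name the same grades as the body.

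The second statement and the abstract correction are changes of text and need no extra pupils. The first raises the minimum by 228 pupils, which the body's grades can supply if school-grades average about 53 (4,728/90 = 52.5).
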